## Abstract

**Introduction::**

Enteric infections caused by *Shigella* and *Campylobacter* species are associated with acute diarrhea as well as enteric dysfunction leading to chronic malnutrition and poor child development. However, interventional studies to reduce exposure to these pathogens have been ineffective, and evidence that identifies putative sources and species transmission dynamics between humans, animals and the environment is scarce. Because isolation of these organisms from both human and environmental samples is challenging, studies using molecular detection may help reduce this substantial knowledge gap and lead to targeted interventions to reduce the burden of disease.

**Methods and analysis::**

This longitudinal cohort study will enroll 100 index infants as well as their families in Haydom, Tanzania. Families will be followed for one year, with collection of stool samples monthly and during incident diarrhea from all household members. Additionally, we will sample from the index child’s environment, including domestic animal stools, drinking water, milk, porridge, flies, and soil. All samples will undergo nucleic acid extraction and quantitative PCR for *Campylobacter* and *Shigella*. Serial serologic tests will also be performed to identify seroconversion to these pathogens. Associations between pathogen detection from the environment and household members and detection in index children will be estimated, and the temporal patterning of infection cases will be analyzed using transmission models.

**Ethics and dissemination::**

This trial has been approved by the Tanzanian National Institute for Medical Research and the University of Virginia Institutional Review Board.

## INTRODUCTION

Diarrhea is the second leading cause of death in children under five years, accounting for annual mortality of approximately 500,000 globally, with the majority of these deaths occurring in sub-Saharan Africa^[1]^. In addition to acute mortality and morbidity, early and repeated enteric infections have been associated with enteric dysfunction, chronic malnutrition, and impaired cognitive development^[2]^; *Shigella* and *Campylobacter* are the two enteric pathogens that have most consistently associated with these long-term outcomes^[3–5]^. Improvements in water, sanitation, and hygiene are broadly considered to be an important approach to reducing the burden of these pathogens; however, recent large cluster-randomized trials have shown little reduction, particularly of bacterial infections ^[6,7]^.

While the general routes of exposure to enteric pathogens through fecal-oral contact are well known^[8,9]^, there are critical limitations to our understanding of pathogen-specific transmission pathways, especially in young children in low-resource settings where the burden and consequences are highest^[10]^. Isolation of bacterial enteropathogens such as *Campylobacter* and *Shigella* from stool, food, water or other environmental samples using conventional culture media bears significant technical challenges including low sensitivity^[11–13]^. The application of molecular diagnostic detection methods could potentially address these limitations^[14]^.

*Shigella* and *Campylobacter* are model organisms to interrogate transmission ecology because they are thought to lie on opposite ends of the continuum of person-to-person (*Shigella*)^[15]^ to environment-to-person (*Campylobacter*) transmission^[16]^. Estimating the degree to which *Campylobacter* transmission is person-to-person and *Shigella* transmission is environment-to-person will significantly advance our understanding of enteric pathogen transmission dynamics by moving from a broad understanding of fecal-oral transmission routes to pathogen-specific household and environmental pathways of highest relevance. We thus propose to study household and environmental transmission of these two important pathogens by close follow-up of a longitudinal cohort of index children and their families, with frequent collection of human stool, animal feces, and environmental samples, using molecular detection methods to identify *Campylobacter* and *Shigella* in the high-burden setting of Haydom, Tanzania.

## OBJECTIVE

The primary objective of this study is to identify potential sources and routes of transmission for *Shigella* and *Campylobacter*, two important causes of diarrhea in young children, in Haydom, Tanzania, with the goal of identifying targeted interventions to confirm the importance of these pathways and reduce exposure to these pathogens.

## METHODS

### Study setting

The study participants will be recruited from four villages surrounding Haydom, Tanzania. The study area has been extensively described^[10,17]^. In brief, Haydom is characterized by poor road infrastructure in a highland setting and primarily dependent on subsistence agriculture and livestock keeping. The area has a high rate of childhood malnutrition and bacterial carriage, previously linked with poor linear growth^[10]^. Understanding how children and the entire household are exposed to these pathogens through the environment is critical for designing targeted and context-specific interventions. The research team has substantial experience with community recruitment, performance of longitudinal cohort studies, sample collection and processing, and the use of molecular methods for detection of enteric pathogens ^[17,18]^.

### Study design and recruitment

This longitudinal cohort study will recruit index children under one year of age as well as their household members, with enrollment occurring over approximately one year and all households followed for 12 months. The index child and all family members who sleep at the house on an average of 4 or more nights per week will be included in the study. Inclusion criteria are 1) the index child must be living in the home, defined by sleeping at the home on average at least 6 nights per week; 2) the family is not planning to move from the study area in next year; and 3) the index child must be below 1 year of age at a time of enrollment and in the current eligible enrollment age stratum (see enrollment below). They will be excluded from the study if 1) the household already has a child enrolled in the study; 2) the index child has been identified to have a developmental abnormality or congenital disease; 3) maternal age is < 18 years; or 4) the index child routinely receives care outside of the home during the day.

### Sample size and power calculation

Assuming that the source analyses are focused on transmission to the index children, and after accounting for the anticipated accrual goal and drop-out rate, a total of 1500 samples from 100 children (13 non-diarrheal and 2 diarrheal stools per index child on average from recent HDSS data) will be included in the analysis. We assumed a design effect of 1.7 to account for correlation between samples from same child, based on the intraclass correlation coefficient of (ICC) 0.05 for *Shigella* and *Campylobacter* detections within samples from the same child in the MAL-ED study^[2]^. We assume the design effect will be similar across *Shigella* and individual *Campylobacter* species. Assuming that 10% of each type of environmental sample tests positive for the target pathogen and the overall prevalence of pathogen infection is 20%, we would have 80% power to detect a risk ratio of 1.76 for each pathogen species and environmental pathway in a two-sided test with alpha=0.05. The minimum detectable risk ratio at 80% power varies by the proportion of environmental samples that test positive for the pathogen and by alternative assumptions for the design effect (Figure 1). Over a range of plausible design effects and pathogen prevalence in varied environmental sample types, we will have power to detect risk ratios that will identify the most important transmission pathways for *Shigella* and the most prevalent individual *Campylobacter* species.

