#### Human stools

Stool samples will be collected upon enrollment, monthly thereafter, and at the time of diarrhea among the index children or any enrolled household member. To characterize duration of pathogen carriage, stool samples from any individual with study-defined diarrhea will continue to be collected approximately twice-weekly for 4 weeks from illness onset, with a collection window of 48 hours. Each participant will collect and provide 5 g or 5 mL of stool sample. All stool samples will be collected within 6 hours of passage and will be transported on ice followed by storage in the lab at −80 °C until TNA extraction. TNA will be extracted using a 200 mg stool aliquot using the QIAamp Fast DNA Stool Mini Kit (Qiagen, Hilden Germany) per manufacturer instructions.

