#### Soil

A metal spatula will be used to collect a single soil sample (5 – 10mL) in a 50mL conical tube. This will be collected from all non-cement floors from the kitchen, the sleeping area, the living area, and just outside the primary entrance. Soil samples are not collected if the homes have cement floors. Samples will be refrigerated for up to 18 hours before processing. DNA will be extracted from soil samples using the DNeasy Power Soil Pro Kit (Qiagen, Hilden Germany) per manufacturer instructions.

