#### Milk and maize porridge samples

Milk and maize porridge samples will be obtained if they are available in the home on the day of sampling. The caregiver will be asked to serve the milk and porridge or liquid in the way she would give it to the child that day. Up to 5 mL of milk and 10 mL of maize porridge will be collected from the caregiver in a 50mL conical tube. Both milk and maize porridge samples will be placed in a cooler bag with ice packs for transport to the lab. Porridge samples will be homogenized using a bag mixer before DNA extraction. Samples will be refrigerated for up to 18 hours before processing. DNA will be extracted from milk and porridge samples using the QIAamp DNA Mini Kit (Macherey-Nagel, Düren, Germany) per manufacturer instructions.

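### The 1500 samples contain no allowance for drop-out, and the single detectable risk ratio of 1.76 assumes full pairing in every pathway, which the sampling rules do not support for soil, food and animals

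*Protocol article*

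**What the plan says.** All references are to the protocol article.

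- **Sample size and power calculation.** The analysis set is "after accounting for the anticipated accrual goal and drop-out rate, a total of 1500 samples from 100 children", made up of "13 non-diarrheal and 2 diarrheal stools per index child on average from recent HDSS data". Drop-out is mentioned but no rate is given. From these inputs the section concludes that "we would have 80% power to detect a risk ratio of 1.76 for each pathogen species and environmental pathway".
- **Abstract, Methods and analysis.** "This longitudinal cohort study will enroll 100 index infants".
- **Human stools.** "Stool samples will be collected upon enrollment, monthly thereafter, and at the time of diarrhea". The section on study design and recruitment sets follow-up at 12 months.
- **Soil.** "Soil samples are not collected if the homes have cement floors".
- **Milk and maize porridge samples.** These "samples will be obtained if they are available in the home on the day of sampling".
- **Animal feces.** Samples come from up to five domestic animal types, limited to those on the household's compound.

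According to the power section, Figure 1 varies the proportion of positive environmental samples and the design effect. The text does not mention varying the number of paired samples.

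**The concern.** Two statements in the power section do not fit the rest of the article.

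First, a sample count described as net of drop-out equals enrollment times the complete schedule. A reader would take it that losses are already covered, and they are not.

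Second, one detectable RR is claimed for every environmental pathway. A pathway contributes to the comparison only when an environmental sample exists to pair with the child's stool. For soil, food and animals the protocol's own rules make that conditional.

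The Data analysis section ranks pathways by attributable fractions computed from the pathway RRs, and it carries those RRs into the transmission models as informative priors. The scientific question is where each pathogen lies between person-to-person and environment-to-person transmission. The conditional samples are all on the environmental side, while household stools carry no availability condition. A weaker or less precise environmental signal could therefore partly reflect fewer pairs, and a uniform 1.76 would hide that.

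**Working it through.** **1. Where the 1500 comes from**

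- Routine stools per child: 1 at enrollment + 12 monthly = 13, the routine maximum.
- With 2 diarrheal stools: 13 + 2 = 15 per child.
- 100 enrolled × 15 = 1500.
- Design effect: 1 + (15 − 1) × 0.05 = 1.70, the value stated, so it also rests on the complete 15.

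No child is lost and no routine stool is missed at any step.

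**2. Reproducing RR 1.76**

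Inputs from the power section: 1500 samples, design effect 1.7, 10% of environmental samples positive, 20% overall infection prevalence, two-sided alpha 0.05, 80% power.

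- Effective n = 1500 / 1.7 = 882, that is about 88 exposed and 794 unexposed.
- Risk in the unexposed: p0 = 0.20 / (0.9 + 0.1 × RR); risk in the exposed: p1 = RR × p0. At RR 1.76, p0 = 0.20 / 1.076 = 0.186 and p1 = 0.327.

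The article names no formula, so four common ones were solved for RR:

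| Formula | Detectable RR at 1500 | Power at RR 1.76 | Samples needed for RR 1.76 |
|---|---|---|---|
| Wald on log RR | 1.64 | 92% | 1062 |
| Pooled | 1.70 | 85% | 1302 |
| Continuity-corrected | 1.74 | 82% | 1445 |
| Unpooled | 1.785 | 78% | 1584 |

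The stated 1.76 lies inside this spread; the continuity-corrected version is closest. In the last column, the pooled entry is 765.6 effective × 1.7 = 1302. The continuity-corrected entry is 85 exposed (rounded up) × 10 × 1.7 = 1445.

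**3. Effect of drop-out alone (10% assumed)**

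1500 × 0.9 = 1350, with whole children lost and the design effect kept at 1.7. Detectable RR is 1.67 (log RR), 1.745 (pooled), 1.79 (continuity-corrected) and 1.84 (unpooled). Power at 1.76 is 81% pooled and 77% continuity-corrected.

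**4. Effect of fewer pairs in one pathway (availability assumed)**

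The article gives no availability shares. The illustration depends on how samples go missing:

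- *Whole households contribute nothing* (as with cement floors). The design effect stays at 1.7. At 50%, 750 / 1.7 = 441 effective.
- *Visits are missing within households* (as with food not in the home that day). Each child contributes fewer pairs and the design effect falls. At 50%, 7.5 per child gives 1 + 6.5 × 0.05 = 1.325, and 750 / 1.325 = 566 effective.

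| Assumed availability | Missing unit | Effective n | Detectable RR, four formulas | Power at RR 1.76 |
|---|---|---|---|---|
| 75% (1125 pairs) | households | 662 | 1.74–1.93 | 66–82% |
| 50% (750 pairs) | households | 441 | 1.91–2.19 | 49–65% |
| 50% (750 pairs) | visits | 566 | 1.80–2.02 | 59–76% |

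At 50% availability no formula reaches 80% power for 1.76. At 75%, only the log-RR formula does.

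**The case against.** **1.76 is compatible with its inputs.** A reader who tries only the pooled formula gets 1.70 and might infer that the figures do not reconcile. The documents do not support that: no formula is named, and the figure lies within the range of ordinary choices. This objection stands in full.

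**Drop-out hardly matters, and there is some slack.** Four households every two weeks over about 26 periods gives 4 × 26 = 104 enrollment slots, about 4% spare. Twice-weekly convalescent stools come on top of the 1500. The small effect of moderate loss is conceded. But the article does not present the extra slots as an allowance, and they conflict with the stated 100. The convalescent stools are described as serving to measure duration of carriage and are not in the power count. Describing 13 as an average does not help either, since it equals the routine maximum.

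**Pathways are pooled.** Food combines milk and porridge; animals combine several species, in an area described as dependent on livestock. A pathway is empty only when none of its sample types is obtained, so availability for food and animals may be high. This stands, and it is why low shares are used only as illustration. Soil has no substitute sample type, so it is the clearest case.

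**Details belong to the full protocol or analysis plan.** An availability table could well sit there. The point concerns what the article does assert: a count net of drop-out that contains none, and one detectable RR for every pathway.

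**Conclusion.** The point holds in limited form. The 1500 is the full schedule for all enrolled children, so the statement that drop-out has been accounted for is not reflected in the arithmetic. The uniform 1.76 assumes 1500 pairs in every pathway, which the collection rules do not support for the conditional ones, soil most clearly.

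The size depends on numbers the article does not give. RR 1.76 ceases to be supported once a pathway's pairs fall below about 1300 (pooled) to 1445 (continuity-corrected). At an assumed 50% availability the detectable RR rises to about 1.9–2.2 with whole households missing, or 1.8–2.0 with visits missing.

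Two stronger readings should be resisted. A reader might infer that 1.76 is simply not achieved. That does not follow from drop-out, and for the conditional pathways it depends on unknown availability; water and household stools carry no such condition. A reader might also infer that an unsampled pathway will enter the total-quantity exposure as zero. The article nowhere says so.

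**What to change.** In the power section:

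1. State the assumed drop-out rate and the number to be enrolled. Then either restate the evaluable count as 1500 × (1 − loss) or remove the claim that drop-out has been accounted for.
2. Name the power formula behind 1.76.
3. Replace the uniform 1.76 with a short table of detectable RR by pathway at its expected number of paired samples. Recalculate the design effect from the expected pairs per child, separating household-level from visit-level missingness. The baseline questionnaire already records house construction materials and animal ownership, so early enrollment data could supply shares for soil and animals; early monthly visits could do so for food.

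The cost is a few sentences and one small table, with no change to design or data collection. Detectable RRs for the conditional pathways will look somewhat less favorable.

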### Enrollment and follow up

To ensure balance of enrolled ages over seasons of the year, enrollment will be stratified by index child age in 3-month strata (0 – 2 months, 3 – 5 months, 6 – 8 months, and 9 – 11 months). Within each 2-week period, one household with a child in each age group will be enrolled. All enrolled index children and their families will be followed for one year from enrollment with twice-weekly visits to identify diarrhea, fever, and antibiotic use (Figure 2). Household stool and environmental samples will be collected monthly, with additional sampling during and after episodes of diarrhea. Diarrhea will be defined by self- or caregiver-report of three or more loose or watery stools in 24 hours or stool with visible blood.

### Characterization of the home environment

At the baseline visit, a semi-structured questionnaire will be used to assess participant sociodemographic characteristics as well as characteristics of the household environment, such as water and sanitation access, house construction materials, presence of handwashing equipment, animal ownership and housing conditions, and food storage and preparation materials at the baseline home visit.

### Structured behavioral observations to quantify pathogen exposures

During the study period, we will conduct direct serial observations of the index children to quantify the potential exposures to *Shigella* and *Campylobacter* through environmental contacts ^[19]^. At baseline, 6 months, and 12 months of follow-up, 6-hour observations on a single day will be conducted by a field staff member who is familiar with the community. The start time of observations will vary from 6 am to noon. Observation will take place only when the child is awake and not defecating in a latrine. During the period of observation, observer will record every contact between a the index child’s mouth and 1) hands ^[8]^, including 2) animals, 3) human and animal feces, 4) water (drinking and swimming/bathing), 5) food, 6) soil, and 7) potential fomites (including cloth and non-cloth objects). We will also document physical contact with other individuals in the household, specifically contact between the child’s mouth and the mother’s breasts or the mother or other individuals’ hands. Behaviors of the primary caregiver will also be recorded, including frequency and duration of conducting activities such as cooking, eating, cleaning, and interacting with children. To record the duration, frequency, and sequence of these contacts, they will be coded using the tablet-based software LiveTrak ^[19]^.

### Monthly household visits and spot checks

During each monthly visit to collect environmental samples, we will conduct a brief household survey and spot-check to record water, sanitation, and hygiene behaviors and indicators of child exposure. Questions include the frequency of observed child ingestion of soil, child mobility, child breastfeeding and feeding practices, animal ownership, animal confinement, animal feces management, frequency and cleaning of animal-raising locations. Spot check observations will include the presence of water storage containers, handwashing stations, soap at handwashing stations, feces on the floor of the latrine, food storage practices, and animals in living spaces, and animal confinement structures.

### Specimen collection, processing, and extraction

We will collect human stool samples as well as multiple environmental specimens from the domestic immediate environment of the index child. Collection, processing and nucleic acid extraction for each sample type is described below. For all samples, Phocine Herpesvirus (PhHV) will be added prior to extraction to assess extraction and amplification efficiency, extraction blanks will be included to monitor extraction contamination, and extracted total nucleic acid (TNA) will be stored at −80°C until PCR is performed.

#### Human stools

Stool samples will be collected upon enrollment, monthly thereafter, and at the time of diarrhea among the index children or any enrolled household member. To characterize duration of pathogen carriage, stool samples from any individual with study-defined diarrhea will continue to be collected approximately twice-weekly for 4 weeks from illness onset, with a collection window of 48 hours. Each participant will collect and provide 5 g or 5 mL of stool sample. All stool samples will be collected within 6 hours of passage and will be transported on ice followed by storage in the lab at −80 °C until TNA extraction. TNA will be extracted using a 200 mg stool aliquot using the QIAamp Fast DNA Stool Mini Kit (Qiagen, Hilden Germany) per manufacturer instructions.

#### Animal feces

At the time of all environmental sampling, fecal samples will be obtained from up to five domestic animal types (cattle, sheep, goats, pigs, dogs and chickens) that are present on the compound of each household. Like in humans, animal stool samples will be transported to the lab on ice and then stored at −80 °C until TNA extraction. Like in human fecal samples, the TNA will be extracted from a 200 mg stool aliquot using a modified the QIAmp Fast DNA Stool mini kit (Qiagen, Hilden Germany) which includes an initial bead beating step followed by the manufacturer’s protocol.

